## Abstract

Due to the chronic nature of knee osteoarthritis (KOA) self-management is considered an essential part of therapy to improve physical function, activity, pain and quality of life (QoL). Web-based rehabilitation may be a potential innovative mode of patient’ training to guide management compared to usual care, especially with the current restrictions pandemic imposed. Moreover, in order to alter KOA patients’ behavior towards physical activity (PA), it may be more attractive and motivating to combine within their rehabilitation program, outdoor real life local activity that could feasible to be sustained in the future. Aim of the current study is to evaluate the effects of a blended web-based rehabilitation compared with structured PA alone in patients with KOA. This is a randomized multi-center study with two prospective arms. Fifty-six eligible participants with KOA will be recruited from the West Attica region (considered as structurally weak areas). After a comprehensive face-to face training session, participants will follow a 6-week web-based rehabilitation program, consisting of exercise, advice material enhanced outdoor structured PA. The control group will be encouraged to follow the outdoor structured PA alone. Baseline, 6-week and 12-week follow up assessments will be performed. The primary outcome is self-reported physical function as measured by the Knee Injury Osteoarthritis Outcome Score (KOOS). Secondary measures include pain, function (Timed Up and Go Test, Sit to Stand test), PA levels (Lower Extremity Activity Scale, Baecke Scale and pedometer), psychological perspective (Tampa Scale of Kinesiophobia) and health-related QoL (Short-Form 12). Baseline-adjusted Analysis of Variance will be used to test for group differences in the primary and secondary outcomes. The study will evaluate the blended web-based exercise and advice material, enhanced with outdoor PA in many respects compared to the outdoor PA alone so as to promote self-management care programs for KOA patients.

**Trial registration**: Prospectively registered ISRCTN12950684 (27-09-2020).

## Introduction

Knee Osteoarthritis (KOA) is a prevalent, chronic degenerative disease characterised by pain, restricted normal daily activities (ADL) and work absenteeism [1]. Limited activity affects psychological well-being, and quality of life (QoL) [2, 3]. Current care for KOA patients is often not consistent with the clinical guidelines [4–6] recommending strengthening exercises, increase in low impact physical activity (PA) and weight management [7–11]. Alternatively, drug therapy and surgical interventions are over-emphasized and add an economic burden to the Healthcare System [7, 10, 12].

With regards to PA, current guidelines suggest that OA patients should be as physically active as their individual potential and condition allows [13–15]. More specifically, the weekly recommendation for aerobic exercise is 150 minutes of moderate-intensity or 2 days/week of moderate-to-vigorous PA muscle-strengthening exercises [16, 17]. Experiencing benefits from exercise and PA, has shown to shape positive beliefs and motivation towards maintaining activity [18]. Therefore, awareness on self-management, in order to avoid restriction of ADL is essential, as alternatively a vicious circle of inactivity, muscle weakness, weight gain, limited socializing, depression, pain increase and functional impairment has been observed [17, 18].

Despite the positive effects on symptoms [19], exercise-focused programs do not promote sustained behavior change and psychological uplift [20]. Another important limitation of the exercise-focused programs is the low degree of adherence that subjects with chronic OA tend to show [21]. For this reason, other measures i.e. motivational talks, calls are often necessary to improve compliance with these programs. Dynamic facilitators in engaging and sustaining exercise and PA are support by healthcare professionals and community, awareness on the condition, encompassing behavioral interventions, purposeful, enjoyful and flexible modes of PA in chronic pain patients [22]. Web-based rehabilitation could be a more cost-effective option to increase access in structurally weak areas, where appropriate healthcare infrastructure is lacking (healthcare and technology literacy is challenging in addition to poorer social income). Moreover, a great advantage is that it can be performed at a self-determined time, and in a home-based environment, which could enhance adherence and resolve transportation and cost issues. There is mounting evidence that orthopedic technology-assisted rehabilitation has a positive impact on various clinical conditions [23], as well as in KOA [24–27]. More specifically, studies on subjects with KOA that have used a website or an electronic application, as a support, for teaching exercise have shown positive effects for increasing PA [24–30].

Given the above, there is a need for a blended program that encompasses physical and behavioral elements, with purposeful and flexible PA, as well as interplay of self-management and healthcare support strategies to promote a good fit for the care of KOA. The study primarily aims to compare the efficacy of a 6-week web-based rehabilitation program of exercise, advice enhanced with outdoor structured PA to manage pain and physical function in KOA patients compared to outdoor PA program alone; secondarily maintenance of the outcomes at mid-term (12-weeks follow up period) will be examined.

### Hypotheses

The proposed randomized controlled trial (RCT) will test the following three hypotheses: 1) A 6-week blended web-based rehabilitation program will be more efficacious in improving PA levels than a 6-week enhanced outdoor activity program alone immediately following the intervention. 2) A 6-week blended web-based rehabilitation program will be more efficacious in improving pain and self-reported physical function than a 6-week enhanced outdoor activity program alone following the intervention. 3) A 6-week blended web-based rehabilitation program will be more efficacious in improving psychological function, QoL and physical activity levels than a 6-week enhanced outdoor activity program alone at mid-term (12 weeks).

## Materials and methods

### Trial design

This will be an assessor-blinded, parallel group, 2-arm prospective randomized controlled trial (Fig 1). The protocol will conform to SPIRIT guidelines for reporting randomized controlled trial studies (S1 Checklist). The trial has been prospectively registered in the ISRCTN clinical trial registry (ISRCTN12950684/27-09-2020, https://www.isrctn.com/ISRCTN12950684). Ethics approval was granted by the Ethics Committee of the University of West Attica, Greece (49238/09-07-2020).

**Fig 1 pone.0268652.g001:**
[figure not shown]
Schedule of enrollment intervention and assessments. WB-OPA: web-based outdoor physical activity; OPA: outdoor physical activity.

A sample of 56 patients with painful KOA will be recruited from the community of West Attica, Greece. The selection of these municipalities was based on the intention to support weak, relevantly neglected infrastructure and poorer financially resources this region holds. A number of recruitment strategies will be used including (i) advertising through then municipality, community centers, local newspapers, Peristeri KEP Ygeias and University websites, University staff newsletters, and Facebook; (ii) placing brochures and flyers and study posters in medical and physiotherapy clinics; (iii) conducting presentations about knee OA in the local community.

### Participants

#### Eligibility criteria

i. Aged ≥ 45 years; ii. Diagnosis of KOA (Kellgren Lawrence ≥ Grade 1–3); iii. Knee pain for ≥ 3 months; iv. Reporting average knee pain in the last week ≥ 3 on an 11-point Numeric Pain Rating Scale (NPRS); v. ability to write and speak Greek; xi. able to use/access computer or tablet and have access to the internet.

#### Exclusion criteria

Knee surgery within the past 6 months; ii. Planning any back or lower limb surgery within the next 12 months; iii. Current or past (within 3 months) oral or intra-articular corticosteroid use; iv. Systemic arthritic conditions such as rheumatoid arthritis or gout; v. Physiotherapy, chiropractic or acupuncture treatment specifically for the knee within the past 6 months; vi. Inability to walk unaided (assistive device such as cane or walker can be used) as this is necessary for some of the physical testing; vii. Medical condition precluding safe exercise (i.e. uncontrolled hypertension or heart condition); viii. Psychiatric history or cognitive impairment precluding safe compliance to the program; ix. Neurological condition.

### Interventions

During the first face-to-face session (week 1), the physiotherapist (MM) will provide information about KOA and the importance of PA. This introductory session will be scheduled for all participants (both groups) to get familiarized with the webpage environment. Moreover, the journey route of the outdoor walking program, appropriate for each participant will be selected and mutually agreed for both groups. To ensure consistency in content and delivery, the same physiotherapist (with >16 years of postgraduate clinical experience) will take care of the supervision and progression of the program of all participants. Weekly phone supervision to encourage adherence and resolve any issues i.e. potential overload or motivation will be offered to both groups. The weekly dose will be completed for 6 weeks in the community. The participants will be instructed to walk at a moderate level of intensity determined by the Rate of Perceived Exertion Scale (0–10). After completion of the 6-week program (week 7), participants will be encouraged to continue improving PA levels in a second face-to-face session, especially with the walking journey routes, but will not receive any additional intervention till the final follow-up. A final face-to-face appointment will take place in week 12 to support and encourage patients to maintain a PA lifestyle.

#### Blended web-based and outdoor PA program (WB-OPA)

Participants randomized to blended web-based rehabilitation (based on ESCAPE-knee pain online resources) will participate in an exercise-based rehabilitation program designed to improve physical function by integrating exercise, PA, education on the condition, and self-management strategies. ESCAPE-pain stands for Enabling Self-management and Coping with Arthritic Pain using Exercise. It is an evidence-based, cost effective, rehabilitation program for people with chronic OA that combines a progressive exercise program with simple advice strategies on how to self-manage their condition [25, 26]. ESCAPE-pain delivers the NICE core recommendations of exercise and education for the management of OA. The physiotherapist teaching the exercise program to participants has undertaken the accredited ESCAPE-pain course. The blended character of the rehabilitation is based on two components: a) physical exercise delivered via web-based video and outdoor PA, and b) education management strategies delivered again via web-based video. In the introductory face-to face session, individual passwords will be provided to this group in order to register and have access to the rehabilitation program. Participants will be instructed to attend 12 exercise sessions, for 6 weeks, twice weekly. More specifically, participants will perform a 35–40 minutes simple exercise regimen based on pre-recorded video that will progress as they improve. The exercises train elements of joint flexibility, muscle strength, balance, and muscle endurance. Additionally, each week, participants will be encouraged to attend a 5–10 minutes pre-recorded advisory video session by the physiotherapist. The advisory sessions include information on OA related topics, i.e. risk factors, clinical manifestations, feasible strategies like ice, dietary control, pacing, goal setting, and overcoming psychological distress. Table 1 presents the study schedule.

**Table 1 pone.0268652.t001:** Description of the study schedule.

Baseline	• Eligibility criteria assessed by investigator
	• Read patient information letter
	• Sign informed consent
	• Completing baseline assessment measurement
	• Schedule face- to face appointment for week 1
Introductory face-to -face session	• Provision of information on OA, benefits of PA on pain by PT
week 1	• Familiarization patient with webpage environment
	• Registration patient and provide digital codes for entrance in the exercise and education video-material
	• Instruction of exercises of week 1 in the home environment
	• Selection and agreement on outdoor journey route, provide relevant map
	• Instruction of the use of pedometer
	• Instruction of the use/ completion of diary weekly log
	• Determination of goals
	• Video-education session 1
	• Two video home-exercise sessions
	• Schedule phone call for week 2
Week 2- week 5	• Video-education session 2–5
	• Two video home-exercise sessions
	• Completion of log-book
	• Discussion of progress by phone call supervision with PT
	• Schedule phone call for following weeks
	• Schedule appointment for follow-up session of week 6
Week 6	• Video-education session 6
	• Two video home-exercise sessions of week 6
	• Completion of log-book
	• Follow-up assessment measurement week 6 by investigator
	• Face-to-face session with PT to monitor progress, logbook and goals on exercise and outdoor activity, discuss increase of selected outdoor PA
	• Encouragement of continuing exercise and PA
	• Encouragement to ask phone call supervision (at their own will)
	• Schedule a follow-up assessment of week 12
Week 7–11	• Self-selected home exercise
	• Selected outdoor activity (walking route)
	• Schedule appointment for week 12
Week 12	• Final follow up assessment by investigator
	• Face-to-face session with PT to discuss long-term goal and support for maintaining active lifestyle.

In addition to the web-based exercise program, the experimental group will be prescribed to perform thrice weekly a pre-determined walk of 500-800m (a walking dose of 70 minutes per week in separate sessions of at least 10 minutes duration), according to their individual potential. The journey routes selected, based on the distance, safety, comfort and enjoyable paths (i.e. local green parks, pedestrian shopping malls, sports courts) with a relevant map will be provided (with analytic description, photos of key corners, benches for rest etc.). Walking programs are known to have beneficial effects on knee pain and function for people with mild to moderate KOA [27, 31–36].

#### Usual care

Participants randomized to usual care (pragmatic control arm) will be guided to engage PA in their daily routine. In the first session, they will be introduced to the same webpage, where the general information on KOA will be only available for education purposes. Participants will be also guided in this session to select a journey route (mutually agreed) within the community and following the same instructions and parameters as the experimental group with the only difference of a frequency of 5 times weekly. The reason for the increased frequency in this group (5 times per week versus 3 times per week in the experimental group) is to preserve an equal dosage of exercise between groups, (since the experimental group will follow the exercise program twice weekly).

Participants in both groups will continue taking their usual medications and other non-surgical treatments to manage their KOA, and use normal assistive devices such as a cane if needed.

#### Adherence strategies

To increase the likelihood of adherence to the interventions, the following behavioural change techniques and strategies will be used. First, each participant will have a planning session with a physiotherapist of up to 30 min to plan the location, day and time of day for each walk, and reinforce that each walk was moderate intensity in at least a 10 min. Second, regular physiotherapy supervision and monitoring each week with regular phone calls based on patient preference will be offered. If any complication or query should arise, participants could discuss it in the weekly phone calls or contact directly the physiotherapist, and they will be informed of the procedure to follow. Third, each participant will wear a pedometer and record the number of steps taken and time spent walking during each session in a logbook. All participants will complete the daily logbook to record the time (in minutes) spent in activity either walking or exercising in for each walking session over the 12 weeks (Table 2). The physiotherapist will monitor the participant’s logbook at each weekly supervisory session (by phone). Fourth, participants will be encouraged to engage social supports such as walking with a friend, family member if they chose to. They will also describe any changes to their usual care of their KOA and any problems with their knee while doing their walking program each week.

**Table 2 pone.0268652.t002:** Logbook diary to monitor compliance, duration and frequency of exercise and outdoor walking activity weekly.

	Week 1		Week 2		Week 3		Week 4…	..Week 10	Week 11	Week 12
	Exercise (-/min)	Walking (-/min/step)	Exercise (-/min)	Walking (-/min/steps)	Exercise (-/min)	Walking (-/min/steps)	Exercise (-/min)	…	…	Walking (-/min/steps)
Monday										
Tuesday										
Wednesday										
Thursday										
Friday										
Saturday										
Sunday										

Participants in both groups will be free to withdraw from the study at any time, but the withdrawal rates and reasons will be recorded.

### Outcomes

#### Primary outcome measures

Outcome measures have been selected based on those recommended for clinical trials of OA [37–39].

a)Physical function: the Knee Injury Osteoarthritis Outcome Score (KOOS) Likert version, which is a disease-specific instrument with good psychometric properties demonstrated in range of OA studies [38, 40]. The KOOS includes 42 items in 5 separately scored subscales: Pain, Other Symptoms, ADL, Function in Sport and Recreation (Sport/Rec), and Knee related QoL.b)Pain: NPRS week Average knee pain over the previous week measured by a valid and reliable Numerical Pain Rating Scale pain with terminal descriptors 0 (no pain) and 10 (worst possible pain and has been shown to be preferred by patients with chronic pain NPRS over other measures of pain intensity, including the VAS, due to comprehensibility and ease of completion [41, 42].

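### The primary outcome is contradictory and not uniquely identified: pain is secondary in the Abstract but primary in the Methods, and no KOOS function score is chosen

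*Protocol article*

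**What the plan says.** - **Abstract.** One primary outcome: "The primary outcome is self-reported physical function as measured by the Knee Injury Osteoarthritis Outcome Score (KOOS"). Pain is placed in the next tier: "Secondary measures include pain, function (Timed Up and Go Test, Sit to Stand test").
- **Primary outcome measures.** Two lettered items stand under this heading. Item (a) is "Physical function: the Knee Injury Osteoarthritis Outcome Score (KOOS) Likert version". Item (b) is "Pain: NPRS week Average knee pain over the previous week". Of KOOS the section says: "The KOOS includes 42 items in 5 separately scored subscales: Pain, Other Symptoms, ADL, Function in Sport and Recreation (Sport/Rec), and Knee related QoL". It selects no subscale and defines no composite.
- **Introduction, final paragraph.** The primary aim concerns pain and physical function with the 6-week programme. Maintenance at 12 weeks comes second.
- **Hypotheses.** The first concerns physical activity: the blended programme "will be more efficacious in improving PA levels than a 6-week enhanced outdoor activity program alone immediately following the intervention". The second joins pain with self-reported function. Physical activity is listed under Secondary outcome measures.
- **Sample size.** 22 per arm for 80% power at a two-tailed 5% level to detect a 15% difference in the KOOS physical function measure, raised to 56 in total for 20% dropout. The margin is traced to a 10-unit difference on a score called both the KOOS-pain subscale and KOOS-PS.
- **Statistical analysis.** ANCOVA, adjusted for baseline, on all primary and secondary outcomes.

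**The concern.** Two questions have no single answer in the protocol.

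First, is NPRS pain primary? The Abstract says no and the Methods say yes.

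Second, which number is the KOOS primary outcome? The label is physical function, but the instrument yields five separate scores. ADL and Sport/Rec both fit the label. The sample-size section does not settle the matter, because the score behind its margin carries one name that refers to pain and another that the article does not expand.

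The trial's main claim is at stake. A favourable NPRS result could be reported as a primary success by citing the Methods, and an unfavourable one set aside as secondary by citing the Abstract. Either function subscale could be put forward once the data are known. A reader could not show that any of these choices departed from the protocol. The stated 5% and 80% belong to one outcome, so they are not both secured once there are two or more.

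**Working it through.** **1. The plan's own figure.** The dropout step reproduces: 22/(1 − 0.20) = 27.5, so 28 per arm and 56 in total. The 22 per arm cannot be reproduced, because no SD is given and the base of the 15% is not stated. Solving backwards (two-sample t-test, 80% power, two-sided 5%, n = 22 per arm) gives a standardised difference d = 0.865. That means an SD of 15/0.865 ≈ 17.3 if the difference is 15 points, or 10/0.865 ≈ 11.6 if it is 10 points.

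**2. Number of candidate primary scores.**
- Two: one KOOS score plus NPRS.
- Three: KOOS ADL, KOOS Sport/Rec and NPRS. This is the natural count if KOOS is read as function but no subscale is chosen.
- Six: all five KOOS subscales plus NPRS. This is an upper limit only.

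**3. False-positive rate if any one score can carry the claim, each at two-sided 5%.** Under independence the rate is 1 − 0.95^k:
- k = 2: 1 − 0.9025 = 0.0975
- k = 3: 1 − 0.8574 = 0.1426
- k = 6: 1 − 0.7351 = 0.2649

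For correlated scores I took equicorrelated normal test statistics and computed the chance that at least one exceeds 1.96 in absolute value. The correlations are assumptions, since the protocol gives none.

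| Scores | Independent | Correlation 0.6 | Correlation 0.8 |
|---|---|---|---|
| 2 | 9.8% | 8.8% | 7.8% |
| 3 | 14.3% | 11.8% | 9.8% |
| 6 (upper limit) | 26.5% | 18.7% | 13.9% |

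**4. Power if all primary scores must succeed.** The error rate stays at or below 5%. With two outcomes, each powered at 80%, joint power is 0.80 × 0.80 = 64% if they are independent. It stays below 80% at any correlation short of 1.

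**5. Power if two primaries share alpha by Bonferroni.** Each is tested at 0.025. With d = 0.865 and 22 per arm, power falls from 80% to about 71%. Restoring 80% takes 27 per arm: by the normal approximation d = 0.845 and 2 × (2.241 + 0.842)²/0.845² ≈ 26.6. With dropout, 27/0.80 = 33.75, so 34 per arm and 68 in total.

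**6. One named primary score.** Alpha stays at 5%, and 22 per arm and 56 in total are unaffected by multiplicity.

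**The case against.** The strongest reply is that the intent can be recovered. KOOS is tied to physical function in the Abstract, the Methods and the sample size, so the sentence on five subscales describes the instrument and does not make all five primary. A multiplicity rule is commonly left to an analysis plan, which is not shown here. The Introduction and the second hypothesis join pain with function, which would fit a rule that both must succeed. On the Abstract's reading, the stated 5% and 80% apply directly once the score is named.

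Most of this stands, and it limits the point. A reader might infer more in four ways, none of which the text supports:
- **Six primary scores.** Three of the five KOOS subscales are not function scores, so six is a ceiling and not the natural count.
- **Success at either of two visits.** The Introduction already ranks the end of the 6-week programme first and 12-week maintenance second. The week-12 hypothesis concerns psychological function, quality of life and physical activity. The reference to 12 weeks under Statistical analysis concerns descriptive summaries.
- **A planned any-one-wins rule at 5% each.** This is inferred from the single stated alpha and from ANCOVA on every outcome. It is not written.
- **A third version of the primary outcome in the Hypotheses.** That section labels nothing as primary. Its order is an editorial matter.

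The reply does not remove the contradiction over pain or the missing choice between two function scores. A later analysis plan could choose one reading, but it could not make both published statements true.

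**Conclusion.** The point holds in this limited form. Pain has two incompatible statuses, the KOOS primary score is not identified, and the sample-size margin does not identify it either. This should be corrected before any outcome data are analysed, because it governs the trial's main claim.

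The size depends on a success rule that the protocol does not fix. If any one score suffices at 5%, the false-positive rate is roughly 8% to 14% over two or three candidates and correlations from 0 to 0.8. If all must succeed, the cost falls on power instead. The 71% under a Bonferroni split rests on an effect size solved backwards from 22 per arm, not on a stated SD. If the Abstract's single outcome is meant, the nominal 5% and the planned 80% remain applicable once its score is named, although the 80% cannot be verified without an SD.

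**What to change.** 1. Name one KOOS function score at week 6 as the single primary outcome, in the same words in the Abstract, Primary outcome measures and Sample size.
2. Base the sample-size margin on that same score. State whether it is 15% (and of what) or 10 units, and give the SD. Naming a subscale while the margin belongs to another score would leave the calculation unaligned.
3. Give NPRS pain one status everywhere. One workable choice is the second test in a fixed sequence at 5%, made only if the primary result is significant.
4. Treat the remaining KOOS subscales, physical activity (the first hypothesis) and all week-12 results as secondary, without a confirmatory claim.

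The cost is wording changes, a registry update and the loss of stand-alone primary status for NPRS pain. Multiplicity requires no more participants, although re-basing the margin could change the sample size on its own account. If the sponsor prefers to keep both outcomes as primary, the protocol must say whether either or both must succeed and re-size to match. For two outcomes under Bonferroni, that means about 68 participants instead of 56, on the back-solved effect size.
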